Oral pain/discomfort	The patients will be asked if they have experienced any oral pain/discomfort over the last 3 months (baseline) and since discharge from the index MipAc unit stay until week 16. Responses will be given on a five-category rating scale ranging from “never” (0), “hardly ever” (1), “occasionally” (2), “often” (3), to “very often” (4).^b^
Falls	Number of falls since discharge from the index MipAC unit stay until week 16.
Hospital/MipAC unit admissions	The total count of hospital admissions and readmissions to the MipAC unit since discharge from the index MipAC unit stay until week 16.
Mortality	Mortality in the period from enrolment until week 16.

*Abbreviations**: **MipAC *Municipal in-patient Acute Care

^a^The measurement may be affected by acute conditions present during the MipAC unit stay. Comparison between the intervention and control group will be made at week 16, without adjusting for baseline values

^b^The measurement is anticipated to be minimally affected by acute conditions present during the MipAC unit stay. Comparison between the intervention and control group will be made at week 16, adjusting for baseline values

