### Implementation {16c}

A statistician independent of the study team (Clinical Trial Unit, Oslo University Hospital) prepared the allocation sequence. RAs enrol participants. LRS performs the randomization within Viedoc™ after completion of baseline assessments.

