## Data collection and management

### Plans for assessment and collection of outcomes {18a}

The participants will be assessed during their MipAC unit admission and at the home visit 16 weeks after baseline examinations. We will collect data on diagnoses, comorbidities, medications, and healthcare utilization from various sources: the participant, MipAC unit records, the Norwegian centralized patient journal, hospital records, and home nursing care service records. All personnel collecting data will be properly trained, and the investigators will review data for accuracy.

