#### Secondary outcomes

To compare the intervention and control group with respect to the secondary outcomes, we will employ various statistical methods based on the characteristics of each variable. These methods include ANCOVA for repeated measures of continuous data, logistic regression for binary outcomes, and independent samples *t*-tests for continuous variables that are measured only after 16 weeks. For non-normally distributed variables, we will apply suitable transformations, such as logarithmic or square root adjustments, to improve normality before analyses. Alternatively, these variables may be analyzed using non-parametric tests if transformations do not result in normal distribution. Regarding the secondary outcomes, we will not implement imputation techniques for missing data, nor will we adjust *p* values for multiple testing.

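### Five of the seven secondary outcomes with a baseline value are to be compared without it; the stated reason does not justify this, and the statistical section implies the opposite

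*Protocol article*

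**What the plan says.** Table 1 (Outcomes {12}, Secondary outcomes) has ten rows.

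- Five carry footnote a: handgrip, orthostatic blood pressure, digit span, unstimulated saliva rate and the eight-item visual analogue xerostomia questionnaire. The footnote gives its reason, "The measurement may be affected by acute conditions present during the MipAC unit stay", and then its rule, "Comparison between the intervention and control group will be made at week 16, without adjusting for baseline values".
- Two carry footnote b: the Shortened Xerostomia Inventory and oral pain/discomfort. Their rule is "Comparison between the intervention and control group will be made at week 16, adjusting for baseline values".
- Three (falls, admissions, mortality) carry neither footnote and are counted after baseline.

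On timing, section {18a} says: "The participants will be assessed during their MipAC unit admission and at the home visit 16 weeks after baseline examinations". Section {16c} says that a member of the study team "performs the randomization within Viedoc™ after completion of baseline assessments".

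On methods, the secondary-outcome paragraph of section {20a} says: "These methods include ANCOVA for repeated measures of continuous data, logistic regression for binary outcomes". It then gives independent-samples t-tests to continuous variables that are measured only at week 16. It adds: "Regarding the secondary outcomes, we will not implement imputation techniques for missing data". It makes no correction for multiple testing.

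**The concern.** The footnote treats a noisy baseline as a reason to ignore it. That reason would have force against a change-from-baseline analysis, where noise in the baseline enters the result in full. It has little force against ANCOVA, where the slope on baseline is estimated and shrinks as the baseline becomes less informative. A covariate fixed before allocation cannot carry a treatment effect.

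Two things are at stake. The first is precision for the physical and cognitive measures and for two of the four oral measures. The second is that the document points two ways. An analyst could follow footnote a or section {20a} and call either one prespecified, for outcomes that have no multiplicity control.

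**Working it through.** **Inputs from the protocol.** 350 participants, 175 per arm, 1:1 (sections {8} and {14}); no stratification ({16a}); baseline completed before randomisation ({16c}); no imputation for secondary outcomes ({20a}); a telephone fallback limited to 15D and medication data ({18b}).

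**Assumed.** The baseline to week-16 correlation r is not in the protocol. It is shown over 0 to 0.7.

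**The plan's own figure.** The only stated power is for the primary outcome: at least 80% for a difference of 0.04 with SD 0.13. The standard error is 0.13 × √(2/175) = 0.0139. Then 0.04/0.0139 = 2.88, and Φ(2.88 − 1.96) = 82.1%, two-sided 5%. The figure is reproduced. No power is stated for the secondary outcomes.

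**Precision.** The unadjusted variance of the difference is 2σ²/n. With ANCOVA it is 2σ²(1 − r²)/n, times (N − 3)/(N − 4) = 347/346 = 1.003 for estimating one slope. The unadjusted difference detectable with 80% power is (1.96 + 0.84) × √(2/175) = 0.30 SD; adjustment multiplies this by √(1 − r²). The last column is Φ(2.80/√(1 − r²) − 1.96).

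| r | Variance ratio 1 − r² | Equivalent unadjusted N, 350/(1 − r²) | Detectable difference (SD) | Power where unadjusted is 80% |
|---|---|---|---|---|
| 0 | 1.00 | 350 | 0.300 | 80% |
| 0.3 | 0.91 | 385 | 0.286 | 84% |
| 0.5 | 0.75 | 467 | 0.259 | 90% |
| 0.7 | 0.51 | 686 | 0.214 | 97.5% |

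If the baseline carries no information at all, the cost is the factor 1.003, or 0.3% in variance.

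**Chance imbalance.** The standard error of a baseline difference is √(2/175) = 0.107 SD. An imbalance of 1.96 × 0.107 = 0.21 SD, reached or exceeded in 5% of randomisations for any one variable, shifts the unadjusted estimate by r × 0.21 = 0.06, 0.10 or 0.15 SD at r = 0.3, 0.5 or 0.7. Given that imbalance, the type I error is about 8%, 13% or 21%. Averaged over all randomisations it is still 5%.

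**Loss related to baseline.** A simulation used 4,000 runs, 175 per arm and about 15% lost per arm. Loss was random in one arm and concentrated at low baseline values in the other. The unadjusted estimate was biased by 0.04, 0.06 and 0.09 SD at r = 0.3, 0.5 and 0.7; the adjusted estimate by 0.002 SD or less. This pattern is an illustration; the protocol does not predict it.

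**Consistency.** The continuous footnote-a outcomes are measured in the unit and again at week 16. Under section {20a} they are therefore not variables measured only at week 16, so its wording leads to ANCOVA. Footnote a excludes it.

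**The case against.** The strongest reply is that nothing here is invalid. A week-16 comparison by randomised group, with complete data, is unbiased and keeps its 5% level. It is prespecified with a reason, it concerns secondary outcomes only, and the primary 15D analysis is already adjusted for baseline. All of that stands, so the point is about efficiency and consistency.

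Four practical objections also have substance.

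- Some acutely ill patients may be unable to complete a baseline test. Without imputation, a plain ANCOVA would drop them although they have a week-16 value. The fix needs a rule for this.
- In a logistic model for orthostatic hypotension, adding baseline status changes the odds ratio from marginal to conditional, and the 1 − r² formula does not apply.
- Where section {20a} falls back on non-parametric tests, the ANCOVA gain does not carry over directly.
- Section {20a} lists methods in general terms while Table 1 is outcome-specific, so an analyst could let the table prevail. The wording still needs reconciling.

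The schedule in Fig. 2 is not shown. That all five measures are taken at baseline is inferred from the footnote's own mention of baseline values together with sections {16c} and {18a}.

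A reader might also infer that the two xerostomia instruments, one adjusted and one not, form a second contradiction. They do not. They are different instruments, and judging one to be more sensitive to acute illness is debatable but consistent.

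**Conclusion.** The point holds as a matter of precision and consistency. The reason in footnote a does not justify leaving out a covariate measured before randomisation, and the footnote conflicts with section {20a}. The gain from adjustment ranges from nothing (r = 0, at a 0.3% cost) to roughly half the variance (r = 0.7). Where each outcome falls is unknown, and acute illness will pull r down.

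Three stronger readings are tempting and are not supported:

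- *That most secondary outcomes are affected.* It is five of ten rows, or five of the seven with a baseline value, and two of the four oral outcomes.
- *That about half the information is wasted.* That needs r = 0.7, which the protocol does not give.
- *That any difference between arms in who remains biases the result.* Only loss related to the outcome does so. Adjustment removes only the part explained by that baseline value, so loss through death or unmeasured causes remains.

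The primary analysis is not touched.

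**What to change.** 1. Reword footnote a so that the week-16 comparison adjusts for the baseline value of the same measure.
2. Use ANCOVA for handgrip, blood pressure values, digit span forward and backward, saliva rate and the visual analogue questionnaire, on the transformed scale where section {20a} calls for a transformation.
3. Use logistic regression with baseline orthostatic status for orthostatic hypotension, and label the result a conditional odds ratio.
4. Add a rule for missing baseline values, such as mean imputation or a missing-value indicator, so that nobody with a week-16 value is dropped.
5. Report the unadjusted comparison as supportive.
6. Make the secondary-outcome paragraph of section {20a} agree with the table, and date the change before unblinding.

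No new data are needed. The cost is about one degree of freedom per outcome, one missing-baseline rule, and a conditional odds ratio for the single binary outcome.

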#### Other pre-specified outcomes

We will calculate the carbon footprint of the intervention and usual care by conducting a life cycle assessment based on ISO standards [40]. We will include data such as types and quantities of medications administered, types and quantities of medical equipment used during the MipAC unit stay, number and length of admissions to healthcare facilities, and number of outpatient and GP consultations in the period from discharge until 16 weeks. These data will be converted to carbon dioxide equivalents.

The primary study period will end after 16 weeks. However, we will also evaluate long-term outcomes in terms of mortality rates and admissions to healthcare facilities up to 1 year.

#### Descriptive variables

Demographics and diagnoses according to ICD-10.Charlson Comorbidity Index (CCI) [41].Clinical Frailty Scale (CFS) [42].Oral health: Number of teeth, tooth mobility, number of patient-referred implants, the Revised Oral Assessment Guide [43], and the Mucosal-Plaque Score [44].Medication details: Information on medications utilized at baseline and after 16 weeks, medication discrepancies, changes to medications initiated during admittance and post-discharge, and recommendations on medication adjustments outlined in the discharge letter. Medications will be registered according to the Anatomical Therapeutic Chemical classification system [45].Nutritional status: Measurement of mid-upper arm circumference [46].Details on the MipAC unit stay: Number of attending physicians, length of stay, reasons for admittance, discharge diagnoses, severity of acute illness as assessed by National Early Warning Score 2 (NEWS2) scores [47, 48], and types and quantities of medical equipment used.Post-discharge healthcare service utilization: This will encompass the frequency of consultations with FPs, the number of outpatient visits, and admissions to various healthcare facilities including hospitals, MipAC units, nursing homes, and rehabilitation institutions.

### Participant timeline {13}

The participant timeline is illustrated in Fig. 2.

**Fig. 2 Fig2:**
[figure not shown]
Schedule of enrolment, interventions and assessments

### Sample size {14}

Based on the results of the previous COOP study, we hypothesize a mean difference between groups of 0.04 on 15D, and the standard deviation of the change in 15D from baseline to 16 weeks is assumed to be 0.13 [12]. With inclusion of a total of 350 patients (whereof 175 in the intervention group), the power to detect a difference of 0.04 on 15D will be at least 80% with a significance level of 5% [11].

### Recruitment {15}

The recruitment team combines the clinical expertise of health personnel familiar with the MipAC setting with the research experience of those skilled in clinical trial recruitment. This ensures efficient and effective participant enrolment.

## Assignment of interventions: allocation

### Sequence generation {16a}

The allocation sequence is computer-generated using variable block randomization. Details on block sizes are concealed from study personnel. No stratification factors are used.

### Concealment mechanism {16b}

Participant registration, data collection, and randomization are seamlessly integrated within the Viedoc™ system. The randomization procedure, along with the outcomes of the randomization, is concealed from the blinded RAs within Viedoc™ due to restrictions defined in their user profiles.

### Implementation {16c}

A statistician independent of the study team (Clinical Trial Unit, Oslo University Hospital) prepared the allocation sequence. RAs enrol participants. LRS performs the randomization within Viedoc™ after completion of baseline assessments.

## Assignment of interventions: blinding

### Who will be blinded {17a}

The RA conducting all assessments is blinded to participant allocation. Due to the intervention’s nature, blinding of participants, relatives, or GPs is not feasible. A blinded statistician will analyze the primary outcome.

### Procedure for unblinding if needed {17b}

We do not foresee any circumstances in which the RAs or statistician need to be unblinded.

## Data collection and management

### Plans for assessment and collection of outcomes {18a}

The participants will be assessed during their MipAC unit admission and at the home visit 16 weeks after baseline examinations. We will collect data on diagnoses, comorbidities, medications, and healthcare utilization from various sources: the participant, MipAC unit records, the Norwegian centralized patient journal, hospital records, and home nursing care service records. All personnel collecting data will be properly trained, and the investigators will review data for accuracy.

### Plans to promote participant retention and complete follow-up {18b}

Upon enrolment, participants are provided with both oral and written information about follow-up procedures. Thirteen weeks after baseline examinations, the RA will contact the participants to schedule the 16-week visit. Participants will also receive a reminder call 24 h prior to assessment. Should participants reject to conduct the home visit, they are given the option to submit their 15D scores and medication information by phone. Collected data from participants who withdraw their consent will be deleted if they request so.

### Data management {19}

Non-identifiable source data are paper versions of the Case Report Forms (CRFs). Data will be entered into electronic Case Report Forms (eCRFs) within the Viedoc™ system direct after patient assessments. These eCRFs, designed by the Clinical Trial Unit at Oslo University Hospital, incorporate automatic range checks and missing data alerts to enhance data quality. Information regarding admissions to healthcare facilities, NEWS2 scores and mortality are directly plotted into spreadsheets.

### Confidentiality {27}

Data will be stored on secure, access-restricted research servers at Oslo University Hospital and the University of Oslo. Each participant will receive a unique identification number. The code linking participants to their identification number will be securely maintained within Medinsight, a system for creating customized registers, on access-restricted servers at Oslo University Hospital. Paper-based materials will be securely stored in locked file cabinets within restricted-access facilities, accessible only to authorized researchers within the research group. Only anonymized data will be published. Person-linkable data will be stored until the end of the project on September 5, 2033, and thereafter deleted.

### Plans for collection, laboratory evaluation and storage of biological specimens for genetic or molecular analysis in this trial/future use {33}

N/a. No biological specimens will be collected for future use.

## Statistical methods

### Statistical methods for primary and secondary outcomes {20a}

#### Primary outcome

The primary analysis will utilize an intention-to-treat approach where all subjects will be maintained in the treatment group to which they were initially assigned.

The primary outcome measure 15D is on an interval scale and is expected to be reasonably normally distributed [30, 33]. This measure will be analyzed using Analysis of Covariance (ANCOVA), with 15D score at week 16 as the dependent variable, randomization group as the fixed factor, and baseline 15D score as covariate. A *p* value of less than 0.05 will be considered indicative of the difference between groups being statistically significant. Differences between treatment groups will be estimated using 95% confidence intervals.

#### Secondary outcomes

To compare the intervention and control group with respect to the secondary outcomes, we will employ various statistical methods based on the characteristics of each variable. These methods include ANCOVA for repeated measures of continuous data, logistic regression for binary outcomes, and independent samples *t*-tests for continuous variables that are measured only after 16 weeks. For non-normally distributed variables, we will apply suitable transformations, such as logarithmic or square root adjustments, to improve normality before analyses. Alternatively, these variables may be analyzed using non-parametric tests if transformations do not result in normal distribution. Regarding the secondary outcomes, we will not implement imputation techniques for missing data, nor will we adjust *p* values for multiple testing.

### Interim analyses {21b}

N/a. No interim analysis is planned.

### Methods for additional analyses (e.g., subgroup analyses) {20b}

#### Adjusted analysis of the primary outcome

Variables known or presumed to have a prognostic impact on the outcome will be individually included as covariates in the analysis, alongside baseline 15D score and randomization group. Should the inclusion of these variables alter the effect estimate for the randomization factor with 10% or more, they will be incorporated into a final model that includes all variables demonstrating an effect of this magnitude. The following variables will be subject to such analyses: age, sex, CFS, CCI, and living alone (yes/no).

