### Trial design {8}

This is a randomized, single-blind, controlled, superiority trial. The individual participant constitutes the randomization unit, with allocation distributed in a 1:1 ratio with two parallel groups. The follow-up period is 16 weeks (±2 weeks) for the clinical outcomes. Moreover, we aim to collect data on mortality and admissions to healthcare facilities 1 year following enrolment. A flowchart of the study’s design is shown in Fig. 1.

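### The supplementary adjusted analysis of 15D keeps a prognostic covariate only if it moves the treatment estimate by 10%, so the observed result helps choose the model and strong but balanced predictors can be dropped.

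*Protocol article*

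**What the plan says.** The rule stands in the protocol article under Methods for additional analyses {20b}, Adjusted analysis of the primary outcome. The candidates are age, sex, CFS, CCI and living alone, and they are chosen for their prognostic value: "Variables known or presumed to have a prognostic impact on the outcome will be individually included as covariates in the analysis". Each is tried singly, next to group and baseline 15D. What follows depends on the treatment estimate: "Should the inclusion of these variables alter the effect estimate for the randomization factor with 10% or more", then "they will be incorporated into a final model that includes all variables demonstrating an effect of this magnitude". The section describes no other multi-covariate model.

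Three other places matter.

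- Statistical methods {20a}, Primary outcome, fixes the primary model separately as an ANCOVA with "15D score at week 16 as the dependent variable, randomization group as the fixed factor, and baseline 15D score as covariate".
- Trial design {8} gives "allocation distributed in a 1:1 ratio with two parallel groups", and Sequence generation {16a} adds: "No stratification factors are used".
- Sample size {14} states the planned effect: "we hypothesize a mean difference between groups of 0.04 on 15D".

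**The concern.** A change-in-estimate screen is a tool for finding confounders in observational data. Here allocation is random, so any baseline difference between the groups is due to chance. The reason to adjust is that a variable predicts the outcome and so removes residual variance. The protocol uses that reason to draw up its list and a different one to decide what stays on it.

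Two consequences follow.

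1. The shift that a covariate causes is roughly its chance imbalance times its slope on the outcome. A strong predictor that is well balanced causes little shift and is dropped, although it would still have narrowed the confidence interval.
2. The yardstick is a percentage of the observed treatment effect. The same covariate with the same imbalance can pass when the estimate is small and fail when it is large. The quantity that the adjusted model is meant to check helps decide what the model contains.

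At stake are the precision of the adjusted estimate and the ability to say beforehand which model it comes from. The primary test is not at stake.

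**Working it through.** **Inputs from the protocol article.** Sample size {14}: 350 patients, 175 per group, difference 0.04, SD of change 0.13, significance level 5% (two-sided assumed, as sidedness is not stated), power at least 80%. Section {20b}: five candidates, threshold 10%.

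**The plan's own figure.** A two-sample comparison with 175 per group, difference 0.04 and SD 0.13 has 82.1% power, and 80% needs 166 per group. The stated power reproduces.

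**Size of the threshold.**

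- Standard error of the treatment difference: 0.13 × √(2/175) = 0.0139.
- Threshold if the estimate is 0.04: 0.10 × 0.04 = 0.004, which is 0.004/0.0139 ≈ 0.29 standard errors.
- Threshold if the estimate is 0.01: 0.10 × 0.01 = 0.001.

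**Chance of passing, by hand.** For a covariate with residual correlation r with the outcome, the SD of the shift is about r × 0.0139. With r = 0.4 (assumed) this is 0.0056.

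- Threshold 0.004: 0.004/0.0056 ≈ 0.72, so it passes about 47% of the time.
- Threshold 0.001: 0.001/0.0056 ≈ 0.18, so it passes about 86% of the time.

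The same predictor, equally prognostic, is kept about half the time or nearly always, depending on the observed effect.

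**Simulation.** 8,000 trials per setting, 350 patients, residual SD 0.13 given baseline 15D, five independent candidates. The document gives no covariate-outcome correlations, so these are assumptions. Set A uses 0.1, 0.1, 0.4, 0.3, 0.1 for age, sex, CFS, CCI and living alone; set B uses 0.2 for all five.

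| | Set A | Set B |
|---|---|---|
| **True difference 0.04** | | |
| Strongest covariate kept | 48% | about 19% (each) |
| No covariate kept | 34% | 44% |
| Average SE: baseline only / 10% rule / all five | 0.0139 / 0.0131 / 0.0119 | 0.0139 / 0.0136 / 0.0125 |
| Power: baseline only / 10% rule / all five | 81.3% / 88.5% / 91.7% | 82.1% / 86.2% / 89.1% |
| Mean estimate under the rule | 0.0403 | 0.0407 |
| **True difference 0** | | |
| Strongest covariate kept | 85% | about 70% (each) |
| Rejection rate: 10% rule / all five | 4.2% / 5.1% | 4.2% / 4.9% |

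In set A the weak candidates (r = 0.1) are kept in about 47% of trials when there is no effect and about 6% when it is 0.04.

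**Loss against fixed adjustment at 0.04.**

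- Reported SE, set A: 0.01310/0.01188 = 1.10, so 10% wider. Set B: 0.01362/0.01253 = 1.09, so 9% wider.
- Power: 91.7 − 88.5 = 3.2 points (A) and 89.1 − 86.2 = 2.9 points (B).
- Actual spread of the estimates over trials, set A: 0.01244/0.01189 = 1.05. Set B: 0.01331/0.01260 = 1.06. At this effect the reported SE under the rule is somewhat larger than the true spread, so it errs on the cautious side.

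If the strongest correlation is 0.2 and the others are weaker, less is lost because there is less to gain: the SE is about 1% wider, power is about 1 point lower, and no covariate is kept in up to 74% of trials.

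**The case against.** The strongest case on the other side has four parts.

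- **The rule is pre-specified.** The candidates, the base model, the one-at-a-time procedure, the threshold and the way the final model is built are all written down. That stands: no analyst discretion is visible. What cannot be known beforehand is the covariate set that the procedure will deliver.
- **It is a sensible robustness question.** In an unstratified trial one may ask whether imbalance in any listed variable moves the estimate, and each variable is examined singly. That also stands, but a fixed five-covariate model answers the question without depending on the size of the effect.
- **Selection is not blind to prognosis.** In set A at 0.04 the strong covariate is kept in 48% of trials against about 6% for the weak ones. The rule also recovers part of the available power gain over the baseline-only model: (88.5 − 81.3)/(91.7 − 81.3) = 69% in set A and (86.2 − 82.1)/(89.1 − 82.1) = 59% in set B. This stands and limits the size of the point.
- **The magnitudes are illustrations.** They rest on assumed correlations and normal outcomes, and the simulation leaves out deaths scored 0 on 15D. This stands too; the direction was the same in every setting tried.

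A reader might go further and infer that the trial's primary result is chosen by the data. The documents do not support that: section {20a} fixes the primary ANCOVA, and nothing makes the trial's conclusion depend on the adjusted model. A reader might also infer false positives or bias. The simulation shows 4.2% rejection under no effect and mean estimates within 0.001 of the true 0.04. Nor does almost every variable enter when there is no effect, or almost none when the effect is large: weak covariates enter in about 47% of set A trials at zero, and at 0.04 something is still kept in 66% (A) or 56% (B).

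**Conclusion.** The point holds for the supplementary adjusted analysis only. Covariates chosen because they are prognostic are retained or dropped according to chance imbalance, against a threshold that moves with the observed treatment effect. With the strongest residual correlation assumed between 0.2 and 0.4, and a true difference of 0.04, the strongest predictor is kept in about 19–48% of trials. The reported standard error is about 1–10% wider, and power about 1–3 points lower, than with all five covariates fixed.

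The direction follows from the text of the rule. The percentages depend on correlations that the document does not give. The primary analysis, its type I error and its power are untouched. This is a modest, inexpensive improvement to a secondary model and does not threaten the trial's main inference.

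**What to change.** Delete the 10% rule. Pre-specify one adjusted ANCOVA of week-16 15D on group, baseline 15D, age, sex, CFS, CCI and living alone, with all five covariates entered whatever they do to the treatment estimate. Keep the primary model as it is and report the adjusted estimate beside it. The single-covariate fits can stay as description if the sponsor wants them, provided that they select nothing.

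The cost is about two sentences. The section already commits to analysing all five variables, so no new data are needed. The model uses five of the 350 − 3 = 347 residual degrees of freedom of the primary model, which leaves 342. The change should be made before the allocation is revealed to those who analyse 15D.
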